## Abstract

**Objective:**

To determine the diagnostic accuracy of end-tidal carbon dioxide (ETCO_2_) detection using capnography for verifying the correct placement of nasogastric tubes (NGTs) among adult patients in hospital settings.

**Materials and methods:**

A prospective observational diagnostic study will be conducted. Patients ≥ 18-year-old and requiring the insertion of an NGT will be recruited using a convenience sampling method from 39 general medical and geriatric wards, intensive care units, accident and emergency departments, and subacute/rehabilitation/infirmary wards in 21 acute or subacute/convalescent/extended care hospitals. ETCO_2_ detection by sidestream capnography, which indicates an airway intubation of an NGT when a capnogram waveform or an ETCO_2_ level > 10mmHg (1.33 kPa) occurs, will serve as the index test. The reference standards will be the X-ray performed and pH value of gastric aspiration (pH ≤ 5.5) after the index test. Each participant will be included only once. Sensitivity, specificity, positive predictive value, negative predictive value, and area under the receiver operating characteristic curve of capnography will be calculated to assess the diagnostic performance of capnography. The variability in diagnostic accuracy in participants with different characteristics will be explored by using chi-squared or Fisher’s exact tests. The time spent and the cost of the tests will be compared using the paired t-test. All statistical tests will be two-sided with a level of significance set at 0.05.

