An increasing amount of evidence suggests that end-tidal carbon dioxide (ETCO_2_) detection may be a promising method to verify NGT placement [2,6]. Capnography comprises the continuous analysis and recording of CO_2_ in respiratory gases. The placement of the NGT within the airway is defined as the detection of ETCO_2_ levels exceeding 15 mmHg (2 kPa) [12–15]. An NGT is also considered to be placed in the respiratory tract if a change from purple to yellow is detected by a colorimetric ETCO_2_ device [14]. We conducted a meta-analysis of nine studies involving 651 NGT placements and found that the pooled results for sensitivity and specificity of ETCO_2_ detection in differentiating respiratory and gastrointestinal (GI) placement of NGTs among critically ill adult patients were high, both of which were 0.99 [16]. After a comprehensive search of databases from 2009 to March 2021, the review was updated, and seven new studies were identified. Of the 16 included studies with 1,878 NGT placements, the pooled results for sensitivity and specificity were 0.96 and 0.99, respectively [17]. The results consistently suggest that capnography and colorimetric capnometry may be of comparable diagnostic accuracy to radiography in their ability to differentiate between respiratory and GI tube placement in critically ill adult patients. However, the limited number of studies conducted in general wards and other hospital settings renders the determination of diagnostic accuracy in this patient population uncertain [13,18].

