### Test methods

#### Index test

Capnography, which monitors ETCO_2_, the percentage concentration, or partial pressure of CO_2_ at the end of exhalation, will serve as the index test. It will be performed by connecting the end of the NGT with the sensor of the bedside sidestream capnography device (Medtronic Capnostream 35 Portable Respiratory Monitor) through an adapter [22]. After connecting the NGT to the sensor, the ETCO_2_ level should be read after a minimum of six breaths or one minute to avoid confusion resulting from CO_2_ in the stomach [13,18,23,24]. Placement within the airway is defined as detecting a capnogram waveform or an ETCO_2_ level > 15 mmHg (2.0 kPa) [15].

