### Data collection

The DN will record the result of ETCO_2_ detection (i.e., presence of any capnographic waveform and ETCO_2_ value and the number of index tests performed per participant) and follow up with the X-ray and the pH test results; and location of NGT (stomach, esophagus, or tracheobronchial tree). These results will be recorded on the data collection form.

The DN will also collect participants’ demographic and clinical data (S1 File), including age, gender, setting (ward/unit and type of hospitals), principal medical diagnosis, reasons for current AED visit or hospitalisation, past medical and surgical history, level of consciousness (assess using Glasgow Coma Scale), level of fitness or frailty (assess using Clinical Frailty Scale), respiration status and support, indication for NGT insertion, type of NGT, mode, amount and frequency of enteral feeding, type of diet or enteral formula, fluid and food intake within 6 hours before NGT insertion, medications administered within 12 hours of NGT insertion, results and duration of the index test and reference test/s performed, complications or adverse events associated with insertion and the testing (index test and reference test/s), cost of the index test, and cost of the reference test/s used.

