## Data analysis

The sample size is determined to give the study adequate precision to estimate the sensitivity and specificity of using capnography in detecting the placement of NGTs using the reference standards of measurement of radiography and aspirates for pH value. In anticipation of sensitivity and specificity of values greater than 90% [17], a sample size of at least 500 participants would be sufficient to estimate these parameters with a margin of error of at most ±3% at a significance level of 0.05. The sample size calculation was performed using PASS 16 (NCSS, Kaysville, USA). Eligible participants will be evenly recruited from the 39 participating wards/units. The target sample size will therefore be rounded up to 507 with 13 eligible participants per each of the 39 wards/units.

IBM SPSS 26.0 (IBM Crop., Armonk, NY) will be used to conduct the data analysis. Participants’ demographic and clinical characteristics will be presented by appropriate descriptive statistics, including mean ± standard deviation, median (inter-quartile range), and percentages for normally distributed, skewed continuous, and categorical variables respectively. Any cases with missing data on the index test or the reference standard results will be excluded from the test accuracy analysis. The true positives (i.e., NGT placements that are tested positive by both index test and reference test/s), false negatives (i.e., NGT placements that are tested negative by index test but positive by reference test/s), true negatives (i.e., NGT placements that are tested negative by both index test and reference test/s), and false positives (i.e., NGT placements that are tested positive by index test but negative by reference test/s) will be calculated, based on which the sensitivity, specificity, positive predictive value, and negative predictive value of the capnography test will be calculated with reference to a combination of X-ray and aspirate pH test using the following formulas:

$$\text{Sensitivity}:\;\text{True}\;\text{Positive}/\left(\text{True}\;\text{Positive}+\text{False}\;\text{Negative}\right)\times 100\%$$

$$\text{Specificity}:\text{True}\;\text{Negative}/\left(\text{True}\;\text{Negative}+\text{False}\;\text{Positive}\right)\times 100\%$$

$$\text{Positive}\;\text{Predictive}\;\text{Value}:\text{True}\;\text{Positive}/\left(\text{True}\;\text{Positive}+\text{False}\;\text{Positive}\right)\times 100\%$$

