$$\text{Negative}\;\text{Predictive}\;\text{Value}:\text{True}\;\text{Negative}/\left(\text{True}\;\text{Negative}+\text{False}\;\text{Negative}\right)\times 100\%.$$

The Area Under the Receiver Operating Characteristic Curve (AUC) of capnography will be calculated to assess the overall diagnostic performance of capnography. The test accuracy level is considered high when the AUC value is ≥ 0.9 [25].

The variability in diagnostic accuracy in participants from different age groups, gender, level of consciousness, level of frailty, type of illness, respiration status and support, drug use, fluid or food intake, types of hospitals and units will be explored by using chi-squared or Fisher’s exact tests, as appropriate. The time spent and the cost of the index test (capnography monitoring) and the reference tests (radiography and aspirate pH test) will be compared using the paired t-test. All statistical tests are 2-sided with level of significance set at 0.05. All cost data will be expressed in Hong Kong and US dollars and the procedural time will be expressed in hours and minutes.

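### The index test is positive above 10 mmHg in the Abstract but above 15 mmHg in the Index test section, and nothing reconciles the two

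*Protocol article*

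**What the plan says.** The article states the rule for a positive index test twice, with different values.

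- Abstract, Materials and methods: an airway intubation is indicated "when a capnogram waveform or an ETCO_2_ level > 10mmHg (1.33 kPa) occurs".
- Methods, Index test: "Placement within the airway is defined as detecting a capnogram waveform or an ETCO_2_ level > 15 mmHg (2.0 kPa").

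The Introduction gives a background definition with citations: "The placement of the NGT within the airway is defined as the detection of ETCO_2_ levels exceeding 15 mmHg (2 kPa"). It agrees with the Index test section.

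Under Data collection, the designated nurse records the "presence of any capnographic waveform and ETCO_2_ value and the number of index tests performed per participant". Under Data analysis, the four cells of the accuracy table rest on whether the index test is positive; a false positive, for example, covers "NGT placements that are tested positive by index test but negative by reference test/s". That section restates no cut-off. The article does not label either value as secondary or as a sensitivity threshold. Fig 1 is not reproduced in the text at hand and could not be checked.

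**The concern.** The positivity rule of the index test is the central definition in a diagnostic accuracy study. Here it takes two values, so the same recorded reading can enter the table as positive or negative depending on the section followed.

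Two things are at stake. First, a reader of the results could not tell from this article which rule the reported accuracy describes, although the study is meant to inform guideline updates. Second, because the raw reading is stored, the cut-off can be applied at analysis, when X-ray and pH results are known. With both values in print, either could then be presented as pre-specified. Lowering the level from 15 to 10 mmHg can only raise sensitivity or leave it unchanged, and can only lower specificity or leave it unchanged. A choice made after seeing the data could therefore favour whichever measure looks better.

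**Working it through.** **1. Are the two values a unit slip?** With 1 mmHg = 0.133322 kPa:

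- 10 × 0.133322 = 1.333 kPa (Abstract: 1.33)
- 15 × 0.133322 = 2.000 kPa (Index test: 2.0)

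Each pair is internally consistent, so the conflict is not a conversion error. That does not rule out an outdated value left in one place.

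**2. Does the sample size depend on the cut-off?** The plan calls 500 participants "sufficient to estimate these parameters with a margin of error of at most ±3% at a significance level of 0.05", for values above 90%. Take p = 0.90, d = 0.03, z = 1.96 and 500 as the denominator:

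- Wald: n = z²p(1−p)/d² = 3.8416 × 0.09 / 0.0009, giving 385.
- Exact (Clopper-Pearson) with the wider, lower arm at most 3 points: n = 492.
- At n = 500 the Wald half-width is 2.63 points and the exact lower arm is 2.97 points.
- 39 × 13 = 507.

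The stated figure is reproduced on that denominator. No ETCO2 cut-off enters it, so it is the same under either rule.

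**3. Which placements change class?**

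| Recorded result | Abstract rule | Index test section rule |
|---|---|---|
| Waveform present, any level | positive | positive |
| No waveform, up to 10 mmHg | negative | negative |
| No waveform, above 10 and up to 15 mmHg | **positive** | **negative** |
| No waveform, above 15 mmHg | positive | positive |

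Only the third row differs. Its size is not given and cannot be derived from the article.

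**4. Shift per reclassified placement.** Let k be the number of airway placements among 507. The article does not give k, so 10, 20 and 50 are assumptions.

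- A reference-positive case moves between false negative and true positive, so sensitivity changes by 100/k points.
- A reference-negative case moves between true negative and false positive, so specificity changes by 100/(507 − k) points.

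| k | Sensitivity, points per case | Specificity, points per case |
|---|---|---|
| 10 | 10 | 100/497 = 0.20 |
| 20 | 5 | 100/487 = 0.21 |
| 50 | 2 | 100/457 = 0.22 |

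**5. Predictive values, for scale.** Take the pooled 0.96 and 0.99 from the Introduction as sensitivity and specificity under the higher cut-off. PPV = TP/(TP + FP), and one reclassified non-airway case adds 1 to FP.

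| k | TP | FP | PPV | PPV with one more FP |
|---|---|---|---|---|
| 10 | 9.6 | 4.97 | 65.9% | 9.6/15.57 = 61.7% |
| 20 | 19.2 | 4.87 | 79.8% | 19.2/25.07 = 76.6% |
| 50 | 48 | 4.57 | 91.3% | 48/53.57 = 89.6% |

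One case therefore costs about 4, 3 or 2 points of PPV. At k = 10, five such cases would take PPV to 9.6/19.57 = 49%, but nothing in the article says whether the number is nearer zero or five. NPV barely moves: one airway case changes it by about 100/492 = 0.2 points at k = 10.

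For comparison, the 95% half-width of specificity at 99% with 497 placements is 1.96 × √(0.99 × 0.01/497) = 0.9 points. About five reclassified non-airway cases (5 × 0.2 = 1.0) would be needed to exceed it.

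**The case against.** The strongest reply is that the Methods hold the operative definition, with a citation, that the Introduction agrees with it, and that the Abstract alone differs. The waveform criterion is common to both rules, so the discordant group may be very small or empty. The waveform and the reading are both recorded, so either rule can be applied to every participant. An AUC built on the recorded ETCO2 value would not depend on the cut-off.

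Much of this stands, and it limits the size of the point. It does not remove the contradiction: both statements are current, and the article does not say which governs.

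Several stronger readings are tempting but unsupported:

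- A reader might infer that the cut-off decides every cell of the table. It does not. A waveform settles the result alone, and readings up to 10 or above 15 mmHg are classified alike.
- A reader might infer that any airway placement reading between 10 and 15 mmHg shifts sensitivity. Only those without a waveform do. The 10-point shift also requires k = 10, which is an assumption.
- A reader might infer that wards are working to different rules. Nothing shows this. The investigators train every designated nurse, who must pass a quiz and is observed once, and the raw values are kept. The main exposure is at analysis.
- A reader might count the Introduction as a third conflicting statement. It is background and agrees with the Index test section.
- A reader might infer that the cut-off will be chosen to flatter the results. The text leaves that possible and gives no evidence of intent.

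**Conclusion.** The concern holds as an internal contradiction in the index-test definition, between the Abstract and the Index test section. It should be corrected because the definition is wrong as written; the case does not rest on a demonstrated large effect.

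The reach is limited to placements with no waveform and a reading above 10 and up to 15 mmHg, whose number is unknown and may be small. Sensitivity is the more fragile measure if airway placements turn out to be few. Specificity would need several reclassified cases before the shift exceeded its own sampling error. These sizes rest on the assumed range of k, and the PPV figures also on the pooled accuracy values. The sample size is unaffected. Which cut-off is clinically right is not judged here.

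**What to change.** Reconcile the Abstract and the Index test section to one primary cut-off, stated identically in both, and fix it in a dated record before any index result is compared with the reference standard. Check that the training material, the data collection form and Fig 1 carry the same value. The Introduction needs no change on this account unless the study's definition departs from it, in which case a sentence should say so.

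Optionally, because the ETCO2 value is already collected, report the other cut-off as a single pre-specified sensitivity analysis, with the count of no-waveform readings above 10 and up to 15 mmHg. Readers could then see how many placements the choice affects.

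The cost is a one-line correction and a document check, with no extra participants or measurements.

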**Discussion:**

This study will provide evidence on the diagnostic accuracy of capnography in verifying NGT placement and its applicability to patients in hospitals settings, since this evidence is limited in the current literature. In addition, it will help identify the optimal combination of tests in verifying the correct placement of NGTs and inform the update of clinical practice guidelines and stakeholders’ decisions on the adoption of ETCO_2_ detection as a routine method for verifying NGT placement.

**Trial registration:**

ClinicalTrials.gov ID: NCT05817864.

## Introduction

Nasogastric tube (NGT) placement is a common practice in hospital settings for assessment, nutrition support, and administration of medication [1,2]. Unfortunately, misplacement of NGTs is common, with an estimated 60% of misplacements resulting in detrimental effects [3,4]. In fact, in over 80% of these misplacements the NGTs were placed in the respiratory tract, leading to serious pulmonary complications, including aspiration pneumonia or respiratory failure [4,5]. Chest/abdominal X-ray is the gold standard for verifying correct NGT placement in the stomach. However, radiography is not always available conveniently at the bedside [6]. Other methods for verifying NGT placement include biochemical measurements of aspirates for pH value or presence of bilirubin, trypsin or pepsin, spring gauge pressure manometer, magnetic detection, ultrasonography, auscultation, and visual inspection of aspirates [7–11]. Factors often compromised the accuracy of these methods include the inability to aspirate adequate fluids for testing, difficulty in visually differentiating the colour change in test strips, use of antacids, reflux of gastric contents, or patients with altered level of consciousness [7,8,11]. Therefore, a reliable and effective bedside test to verify NGT placement is required.

An increasing amount of evidence suggests that end-tidal carbon dioxide (ETCO_2_) detection may be a promising method to verify NGT placement [2,6]. Capnography comprises the continuous analysis and recording of CO_2_ in respiratory gases. The placement of the NGT within the airway is defined as the detection of ETCO_2_ levels exceeding 15 mmHg (2 kPa) [12–15]. An NGT is also considered to be placed in the respiratory tract if a change from purple to yellow is detected by a colorimetric ETCO_2_ device [14]. We conducted a meta-analysis of nine studies involving 651 NGT placements and found that the pooled results for sensitivity and specificity of ETCO_2_ detection in differentiating respiratory and gastrointestinal (GI) placement of NGTs among critically ill adult patients were high, both of which were 0.99 [16]. After a comprehensive search of databases from 2009 to March 2021, the review was updated, and seven new studies were identified. Of the 16 included studies with 1,878 NGT placements, the pooled results for sensitivity and specificity were 0.96 and 0.99, respectively [17]. The results consistently suggest that capnography and colorimetric capnometry may be of comparable diagnostic accuracy to radiography in their ability to differentiate between respiratory and GI tube placement in critically ill adult patients. However, the limited number of studies conducted in general wards and other hospital settings renders the determination of diagnostic accuracy in this patient population uncertain [13,18].

To determine the applicability of ETCO_2_ detection in clinical settings, Cheng and Lee evaluated the diagnostic accuracy of colorimetric capnometry in verification of feeding tube placement in 26 patients (with 71 doubtful NGT placements) recruited from three medical extended wards in a public hospital in Hong Kong [13]. The specificity of the colorimetric capnometry was 98.6%, while the sensitivity could not be determined. A team of community nurses conducted a pilot study between March and April 2021 to examine the use of capnography in verifying correct NGT placement. Two devices were used, namely EMMA Capnograph and Rad-97 Pulse Co-oximeter. A total of 12 older adults (mean age 80.3 years, range 55–89 years old) residing in old age homes were recruited. Nine of them were receiving lansoprazole, and one was receiving famotidine. Of the 15 episodes of NGT insertion performed among the 12 older adults (seven used EMMA Capnograph and eight used Rad-97), none of the episodes detected ETCO_2_ and crisp waveforms after testing of tube placement in the stomach by the Whoosh test [13].

Despite the potential benefits, some gaps regarding the use of ETCO_2_ detection were identified in the literature. First, the majority of included studies in the two meta-analyses examined critically ill patients or patients with mechanical ventilation [16,17]. Also, the two studies in Hong Kong were conducted among a small sample of hospital patients and community-dwelling older adults. Thus, there is limited evidence on the diagnostic accuracy of ETCO_2_ detection in acute and rehabilitation settings, particularly general wards, accident and emergency departments (AEDs) and intensive care units (ICUs). Second, the sensitivity and specificity of ETCO_2_ detection shown in the meta-analyses were less than 100%. Factors such as recent ingestion of carbonated fluids or poor connection between NGTs and ETCO_2_ detectors may result in false positive or false negative results [16,17,19]. Therefore, further examination of strategies to enhance the diagnostic accuracy of ETCO_2_ detection is needed. A protocol on the procedure of carrying out ETCO_2_ detection is also needed to avoid the possibility of false results caused by mal operation of the device or tubing misconnections. Third, ETCO_2_ detection is suggested to be effective only in differentiating between respiratory and GI placement of the NGTs. The use of this method to verify correct tube placement in the stomach, either alone or in combination with other index tests or reference standards, is yet to be determined. Thus, this study aims to discern the diagnostic accuracy of ETCO_2_ detection using capnography in verifying the correct placement of NGTs among adult patients in hospital settings.

## Materials and methods

### Study design

A prospective observational diagnostic study will be conducted to assess the sensitivity and specificity of capnography in detecting the correct placement of NGTs using the reference standards of radiography and measurement of aspirates for pH value. This study was registered with ClinicalTrials.gov (ID: NCT05817864). We reported this study protocol following the recommendations of the STARD (Standards for Reporting Diagnostic Accuracy) statement [20] and the SPIRIT (Standard Protocol Items: Recommendations for Interventional Trials) 2013 statement [21].

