#### Reference standard

The reference standard is the test, series of tests, or set of procedures used to determine the presence or absence of the target condition in individuals, which in this study is airway intubation of an NGT [25]. This study will use radiography (chest/abdominal X-ray) as the reference standard for determining the correct placement of NGTs. Radiology will be performed as soon as possible and interpreted by a physician. A repeat radiography will be performed if necessary. We will also use pH-Fix-4.5–10 to determine the pH value, and its accuracy is +/- 0.2 with minimum increments of 0.5. A pH of 5.5 or below indicates gastric placement [2].

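### The stated aim is accuracy for correct placement but the stated target condition is airway intubation, so oesophageal tubes have no fixed cell in the primary 2×2 table

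*Protocol article*

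**What the plan says.** The Study design section of the protocol article states the purpose as "to assess the sensitivity and specificity of capnography in detecting the correct placement of NGTs". The Abstract objective, the end of the Introduction and the opening of the Discussion describe the aim in similar terms.

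The Reference standard section defines the target condition differently: "which in this study is airway intubation of an NGT". Its next sentence uses X-ray "as the reference standard for determining the correct placement of NGTs", and it then adds a pH rule: "A pH of 5.5 or below indicates gastric placement".

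The index test points to the airway. The Index test section says "Placement within the airway is defined as detecting a capnogram waveform" or an ETCO2 level above a threshold, and the Abstract gives the same direction.

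The Data analysis section defines true positives as "NGT placements that are tested positive by both index test and reference test/s", with X-ray and pH combined as the reference. It does not tie reference-positive to a location. The Data collection section does record "location of NGT (stomach, esophagus, or tracheobronchial tree"), so the oesophagus is a separate category, but no section assigns it to a cell.

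The Introduction acknowledges a limit of the test: "ETCO_2_ detection is suggested to be effective only in differentiating between respiratory and GI placement of the NGTs".

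**The concern.** Two target conditions stand in the current text, and they treat one group of tubes in opposite ways. Capnography is expected to show no CO2 in an oesophageal tube. If the question is whether the tube is in the airway, that result is right. If the question is whether the tube is correctly placed, and correct means in the stomach, the same result is a missed misplacement.

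The combined reference adds to the problem. X-ray can separate all three locations. The pH rule speaks only to gastric placement and cannot tell airway from oesophagus. Including pH pulls the reference towards stomach or not, while the stated target condition pulls it towards airway or not.

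The primary 2×2 table, and every estimate taken from it, depends on the choice. The Discussion says the results will inform Hospital Authority guidance. A high figure labelled as accuracy for correct placement could be taken as evidence of gastric position, which the Introduction treats as still undetermined.

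**Working it through.** **Inputs**
- CO2 detected in 96% of airway tubes and 1% of gastrointestinal tubes. This is an illustration from the pooled sensitivity of 0.96 and specificity of 0.99 in the Introduction. The 1% is assumed to apply equally to oesophagus and stomach.
- Share of misplaced tubes that are oesophageal, *f*. The protocol gives no misplacement rate for its population. The Introduction reports over 80% of misplacements as respiratory. From the sentence before it, that may describe harmful misplacements only, and it does not say that the rest were oesophageal. Values of *f* are therefore assumptions.
- Planning figures from Data analysis: at least 500 participants, margin of at most ±3 points, sensitivity and specificity above 90%, final target 507.

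**The plan's own figure**

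At a proportion of 0.90, the Wald half-width with 500 in the denominator is 1.96 × √(0.90 × 0.10 / 500) = 0.026, or 2.6 points. The Wald formula needs 385 for ±3 points. An exact interval with its lower limit within 3 points needs 492. The stated 500 is therefore adequate for a parameter whose denominator is all 500.

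**Effect of the target condition on sensitivity**

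With a CO2 signal as index-positive:
- Target airway: sensitivity = 0.96, and oesophageal tubes without CO2 are true negatives.
- Target not in the stomach: sensitivity = 0.96(1 − *f*) + 0.01*f* = 0.96 − 0.95*f*, and those same tubes are false negatives.

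| Assumed mix | *f* | Sensitivity, airway | Sensitivity, not in stomach |
|---|---|---|---|
| No oesophageal tubes | 0 | 96% | 96% |
| 80% airway, 20% oesophageal | 0.20 | 96% | 0.96 − 0.19 = 77% |
| 2% of all tubes airway, 1% oesophageal | 1/3 | 96% | 1.93 / 3 = 64% |
| 2% of all tubes airway, 3% oesophageal | 0.60 | 96% | 1.95 / 5 = 39% |

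Specificity is 99% under both targets. Only its denominator changes: oesophagus plus stomach for airway, stomach alone for not-in-stomach.

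**Precision under the airway target**

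If 2% of 507 tubes are in the airway (about 10, assumed), the half-width at 0.90 is 1.96 × √(0.09 / 10) = 0.186, or about 19 points. With 25 airway tubes it is 1.96 × √(0.09 / 25) = 0.118, or about 12 points.

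**The case against.** The best defence is that the airway reading is already fixed. The target condition is named outright, the Abstract and the Index test section make a CO2 signal mean airway, and the Discussion names detection of respiratory placement as the practical yield. Correct placement could then be the clinical purpose and not the formal target. Much of this stands, and it is why the airway reading should be kept. It does not remove the conflict. The Reference standard section itself gives X-ray the task of showing correct placement, pH in the reference can show only gastric placement, and the Introduction leads into the aim from the open question of verifying gastric position.

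A reader might go further and infer that sensitivity and specificity change places. The documents do not support that. It would require absence of CO2 to count as index-positive, and the Abstract, the Index test section and the true-positive definition in Data analysis together exclude it.

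Nor do the Abstract objective or the Study design section mention the stomach. Reading correct placement as gastric is an inference from the Introduction, the inclusion criteria and the pH rule, though a strong one.

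Finally, an article may leave the coding of locations to a full protocol or analysis plan, and the three locations are recorded, so either analysis can be recovered. That is fair as to detail. The two target conditions, however, are stated in this text, and a later document would have to overrule one of them.

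**Conclusion.** The point holds as a contradiction about the target condition that leaves oesophageal tubes without a cell in the primary table. It affects those oesophageal tubes that show no CO2.

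Under the illustrative 96% and 1% detection rates, sensitivity is 96% for airway and about 77% for not-in-stomach at an 80/20 mix, a gap of 19 points. If more than 80% of misplacements are respiratory in this population, the gap is smaller, and it vanishes with no oesophageal tubes. The 64% and 39% figures need one third and three fifths of misplacements to be oesophageal. They show how the result moves and should not be read as expected values, since the only mix the protocol reports points to a smaller oesophageal share.

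The issue should be settled before results are seen, because a later choice could favour the better-looking figure.

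**What to change.** State one primary target condition, consistent with the Index test section and the stated target condition: reference-positive is tracheobronchial, and reference-negative is oesophagus or stomach. Carry it through Study design, Reference standard and Data analysis.

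Say openly that pH cannot separate airway from oesophagus. Location for the primary table therefore comes from X-ray, and pH is kept for the stomach versus not-stomach analysis. This is a change to the combined reference in Study design and Data analysis and should be declared as an amendment.

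Add a secondary table of index result by the three recorded locations, report stomach versus not-stomach accuracy separately, and make no claim of verified gastric placement from the primary table.

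The cost is wording and one table from data already collected. The downside is that the headline claim narrows to airway detection, and its sensitivity rests on few airway tubes, so the ±3-point margin should not be claimed for it.
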